## **Missing data**

We expect missing data to be Missing Completely At Random. We plan to investigate the possible impact of missing data in sensitivity analyses. Multiple Imputation (MI) is a statistical technique used to handle missing data by creating multiple plausible datasets, analysing each separately, and then pooling the results to account for uncertainty. This approach is particularly useful for sensitivity analyses in cross-sectional descriptive studies, ensuring that findings are robust to different assumptions about missing data. We will also explore the impact of the missing data by applying a best- and worst-case scenario.

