## METHODS

The present study is part of a larger research initiative. Findings on the associations between PD and PD subtypes and pulmonary function test (PFT) measures, thoracic ultrasound, diaphragmatic ultrasound, and additional biomarkers will be reported in separate publications. A separate study will examine PD diagnoses and selected outcomes, including thoracic and diaphragmatic ultrasound, in newly diagnosed systemic lupus erythematosus (SLE) patients. Patients were identified through a systematic search of hospital records across all institutions in the Southern Denmark Region. The search includes visits between July 1, 2021, and June 30, 2023, coded as related to SLE or SLE-associated diseases. Participants were enrolled between August 1, 2023, and October 31, 2024. Statistical analyses will commence upon finalization and approval of this SAP.

At a single visit day all tests were performed. All participants start with an outpatient visit, where the primary investigator review the participants' medical history, note the patients' disease activity and damage. Hereafter the participants undergo pulmonary function testing, HRCT scan, and blood and urine samples. Questionnaires are filled out before the visit. The HRCT scans are described after the visits, and finally the participants are diagnosed, at a multidisciplinary discussion (MDD). The study will be reported in accordance with the STROBE guideline (Strengthening of Reporting Observational Studies in Epidemiology). It is not always possible to measure a precise saturation in a six-minute walk test, why we have scored them as good, medium, poor, too bad to use. Good is tests without any outages. Medium is tests with outages, that which we do not suspect affect the measurement. Poor is tests where we suspect, that the outages affect the results. We will only use tests that score good or medium, and the rests will be regarded as missing values.

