| Tightness in chest, status               |     |            |           |                                 |
| Never, no. (%)                           |     |            |           |                                 |
| Prior, no. (%)                           |     |            |           |                                 |
| Present, no. (%)                         |     |            |           |                                 |
| Pulmonary function tests:         |     |            |           |                                 |
| Body plethysmography:             |     |            |           |                                 |
| FEV 1 , %*                    |     |            |           |                                 |
| FEV 1 low**, no. (%)          |     |            |           |                                 |
| FVC, %*                                  |     |            |           |                                 |
| FVC low**, no. (%)                       |     |            |           |                                 |
| FEV 1 /FVC (ratio)            |     |            |           |                                 |
| FEV 1 /FVC below 70%, no. (%) |     |            |           |                                 |
| TLC, %*                                  |     |            |           |                                 |
| TLC low**, no. (%)                       |     |            |           |                                 |
| Diffusion test:                   |     |            |           |                                 |
| DLCO, %*                                 |     |            |           |                                 |
| DLCO low**, no. (%)                      |     |            |           |                                 |
| KCO, %*                                  |     |            |           |                                 |
| KCO low**, no. (%)                       |     |            |           |                                 |
| 6 min walk test:                  |     |            |           |                                 |
| Distance, %*                             |     |            |           |                                 |
| Distance low**, no. %                    |     |            |           |                                 |

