| Desaturation, (Saturation delta)         |     |            |           |                                 |
| Desaturation below 93% #, no. %          |     |            |           |                                 |

Value will be means and SDs unless otherwise indicated. \* - % of expected; \*\* - low is defined as below 80% of expected; # - If COPD or emphysema 88%. SLE – Systemic Lupus Erythematosus; PROMs – Patient Reported Outcome Measures; PFT – Pulmonary Function Tests; PD – Pulmonary Disease according to multidisciplinary discussion; APL– Antiphospholipid Antibodies; dsDNA – anti-double stranded DNA antibodies; SLEDAI 2K – Systemic Lupus Erythematosus Disease Activity Index 2000 (16); PGA – Physician Global Assessment (17); LLDAS – Lupus Low Disease Activity State (18); DORIS – Definition of

Remission in SLE (19); SLICC DI – Systemic Lupus International Collaborating Clinics /American College of Rheumatology Damage Index for Systemic Lupus Erythematosus (20); LIT – questionnaire inspired by “Lupus Impact Tracker” (21); SLAQ – Systemic Lupus Activity Questionnaire (22); MRC – Medical Research Council Dyspnoea Scale; FEV1 – Forced Expiratory Volume in One Second; FVC – Forced Vital Capacity; TLC – Total Lung Capacity; DLCO - Diffusing capacity of the Lung for Carbon Monoxide; KCO – Carbon Monoxide Transfer Coefficient.

We plan to present the prevalence of subgroups of PD in a table, see table 3.

**Table 3.** Diagnoses of pulmonary diseases among Systemic Lupus Erythematosus patients.

| Groups of PD | Subgroups of PD                 | Prevalence, no. (%) |
|--------------|---------------------------------|---------------------|
| Airway       |                                 |                     |
|              | Asthma                          |                     |
|              | Bronchiectasis                  |                     |
|              | Obliterative Bronchiolitis      |                     |
|              | Infectious Bronchiolitis        |                     |
|              | COPD                            |                     |
|              | Emphysema                       |                     |
|              | Other                           |                     |
| Pleural      |                                 |                     |
|              | Pleuritis                       |                     |
|              | Pleural disease of diaphragm    |                     |

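### The six-minute walk quality rule, as worded, discards valid walking distances along with poor saturation traces, and the blanket MCAR expectation is unsupported for the saturation outcomes

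*SAP*

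**What the plan says.** SAP, METHODS, explains why walk tests are graded: "It is not always possible to measure a precise saturation in a six-minute walk test". There are four grades, from good down to unusable. The two middle grades both have outages and differ only in a judgement about their effect. The one that is kept reads "Medium is tests with outages, that which we do not suspect affect the measurement". The one that is dropped reads "Poor is tests where we suspect, that the outages affect the results". The rule then follows: "We will only use tests that score good or medium, and the rests will be regarded as missing values".

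SAP, Missing data, covers all variables with one sentence: "We expect missing data to be Missing Completely At Random". It places multiple imputation among the sensitivity analyses and adds: "We will also explore the impact of the missing data by applying a best- and worst-case scenario". It gives no imputation model, and it does not define the best and worst case for any variable.

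Table 2, Appendices 1a to 1d and Appendix 3 report four rows under the walk test: distance as a percentage of expected, low distance, saturation delta, and desaturation below a threshold. Appendices 1a to 1d have columns for N. Table 2 and Appendix 3 do not. The closing list of deviations records no change to the grading rule or to the missing-data section.

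**The concern.** Two things do not fit together.

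- **Unit of deletion.** The grade describes the saturation signal, but what becomes missing is the test. Distance is an outcome of the same test and does not need an oximeter. An analyst following the text literally would blank the two distance rows along with the two saturation rows, and lose precision for nothing.
- **Mechanism.** MCAR means that missingness is unrelated to any patient feature and to the value itself. For the saturation rows, some of the missingness is created by the investigators' judgement about the result, with no objective threshold. Nothing in the SAP supports MCAR there. If traces fail more often in patients who truly desaturate, the desaturation percentages and the PD versus no-PD risk differences would be distorted.

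The planned safeguards do not settle the second point. Standard multiple imputation assumes missing at random (MAR), so it does not test for loss that depends on the unseen value. The best/worst case is undefined for a continuous measure such as saturation delta.

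**Working it through.** The SAP states no figure on this point, so there is none to reproduce. The check has a textual part and an illustrative part.

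**Text, side by side**

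| Element | SAP wording concerns | Consequence |
|---|---|---|
| Reason for grading | Saturation precision | Only saturation delta and the desaturation row depend on it |
| Unit set to missing | The test | All four walk-test rows, if read literally |
| Medium versus poor | Suspected effect of outages on the result | Retention rests on judgement |
| Assumed mechanism | All missing data, MCAR | No exception for the judged rows |

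**Illustration 1: desaturation rate.** All inputs are assumptions. Let p be the true share desaturating, m1 the share of desaturators whose trace is dropped, and m0 the share of non-desaturators whose trace is dropped.

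Observed share = p(1 − m1) / [p(1 − m1) + (1 − p)(1 − m0)]

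With p = 0.20 and m0 = 0.10:

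- m1 = 0.10: 0.18/(0.18 + 0.72) = 20.0%
- m1 = 0.20: 0.16/(0.16 + 0.72) = 18.2%
- m1 = 0.30: 0.14/(0.14 + 0.72) = 16.3%
- m1 = 0.50: 0.10/(0.10 + 0.72) = 12.2%

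With p between 10% and 30%, m0 = 0.10 and m1 from 0.10 to 0.50, the bias runs from 0 to −10.8 percentage points. The extreme is p = 0.30 with m1 = 0.50, where 19.2% is observed.

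**Illustration 2: contrast by PD.** Assume true desaturation of 30% with PD and 10% without, a risk difference of 20 points. With m0 = 0.10 in both groups:

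- m1 = 0.20: 27.6% − 9.0% = 18.6 points
- m1 = 0.30: 25.0% − 8.0% = 17.1 points (17.05 before rounding)
- m1 = 0.50: 19.2% − 5.8% = 13.4 points

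The odds ratio does not move under this mechanism. The odds in each group are multiplied by the same factor (1 − m1)/(1 − m0), which cancels. With m1 = 0.50, (0.15/0.63)/(0.05/0.81) = 3.86, the same as the true (0.30/0.70)/(0.10/0.90) = 3.86.

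**Illustration 3: distance.** If a fraction m of distances is deleted needlessly, interval width grows by 1/√(1 − m): 1.026 for m = 5%, 1.054 for 10%, 1.118 for 20%, and 1.195 for 30%.

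**The case against.** The strongest reply is that the grading paragraph opens with saturation and speaks of effects on the measurement, so its natural sense may be that only the saturation reading becomes missing. Appendices 1a to 1d, with their N columns, could carry a different N on each row. This is a fair reading, and nothing in the SAP says that distances have been dropped. It does not settle the matter, because the operative sentence refers to tests and never limits itself to saturation.

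A second reply is that discarding untrustworthy traces is ordinary quality control. The judgement is about whether an outage matters, not about whether saturation is low. That also stands. A reader might infer that sicker patients, or those with poor peripheral circulation, lose their signal more often, and that the desaturation results are therefore biased. The SAP offers no evidence linking outages to low saturation, to PD or to any patient feature. If outages are purely technical, the bias is nil.

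A reader might also conclude that MCAR is the stated ground for a complete-case primary analysis, and that multiple imputation must become primary for all lung-function, walk-test and questionnaire variables. The SAP never names a complete-case analysis. That the main results use available data is an inference from imputation being listed as a sensitivity analysis. The grading rule concerns walk tests only, so it gives no reason to change the handling of other variables. Imputation under MAR would also not remove the value-dependent loss illustrated above.

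Finally, it would be too strong to say that best/worst case cannot be applied to continuous measures. Extreme plausible values can be assigned, but the SAP names none.

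**Conclusion.** The point holds in two limited parts.

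First, as worded, the rule removes walking distances that the oximeter cannot affect. If it is applied literally, the cost is precision: about 3% to 20% wider intervals for an assumed 5% to 30% of tests discarded. If a saturation-only rule was meant, the cost is nil and the wording needs correcting.

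Second, MCAR is unsupported for saturation delta and the desaturation row. Whether that causes bias is unknown. It is nil under equal loss. With 20% true desaturation and 10% loss among non-desaturators, 18.2% to 12.2% would be observed for 20% to 50% loss among desaturators. All of these inputs are assumed. Under that mechanism prevalences and risk differences would shift, while the odds ratios planned in Appendix 3 for the desaturation row would not.

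The reach is limited to walk-test rows in Table 2 and Appendices 1 and 3. The primary result, PD prevalence by multidisciplinary discussion, is not directly affected.

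**What to change.** 1. In METHODS, state that the quality grade applies only to saturation delta and the desaturation row, and that distance is kept for every completed walk.
2. In Missing data, withdraw the MCAR expectation for the saturation variables, and report the number of discarded traces by PD group.
3. Keep the planned multiple imputation, under MAR, as a sensitivity analysis. For continuous saturation delta, add a delta-shift of the imputed values over a stated range. Keep best/worst case for the binary desaturation row.

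Making multiple imputation the primary analysis is optional and not required by this point.

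The cost is a few sentences, one extra count by group and one small sensitivity analysis. No new data are needed, and imputation is already planned. If distances were in fact dropped, the distance rows need to be rerun.

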## **Statistical software**

We will analyse the results with StataBE 18.0 (64bit).

## RESULTS

In the following we show, how we plan to report the results.

We plan to present the trial flow with a flowchart as described in figure 1.

**Figure1.** Flowchart describing the trial flow of possible participants in the study.

[figure not shown]

SLE – Systemic Lupus Erythematosus; HRCT – High Resolution CT scan; 6MWT – Six Minute Walk Test; ILDs – Interstitial Lung Diseases; SLS – Shrinking Lung Syndrome.

We plan to present baseline characteristics, Systemic Lupus Erythematosus activity and damage scores, patient reported outcome measures, and pulmonary function tests, for all patients and stratified according to presence and absence of PD and analyses of differences in the variables according to status of PD, in two tables, see table 1 and table 2.

**Table 1.** Baseline characteristics, for all patients, and stratified according to presence and absence of thoracic diseases

| Baseline characteristics                    | All | PD Present | PD Absent | Std. Difference |
|----------------------------------------------------|------------|-------------------|------------------|------------------------|
| Age, years                                         |            |                   |                  |                        |
| Disease duration, years                            |            |                   |                  |                        |
| Female sex, no. (%)                                |            |                   |                  |                        |
| White population no. (%)                           |            |                   |                  |                        |
| Smoking, composite                                 |            |                   |                  |                        |
| Smoking, status                                    |            |                   |                  |                        |
| Never, no. (%)                                     |            |                   |                  |                        |
| Prior, no. (%)                                     |            |                   |                  |                        |
| Present, no. (%)                                   |            |                   |                  |                        |
| BMI, kg/m                              |            |                   |                  |                        |
| Overlap to other CTDs, composite                   |            |                   |                  |                        |
| Overlap to other CTDs, no. (%)                     |            |                   |                  |                        |
| Sjogren's Syndrome, no. (%)                        |            |                   |                  |                        |
| Rheumatoid Arthritis, no. (%)                      |            |                   |                  |                        |
| Systemic Sclerosis, no. (%)                        |            |                   |                  |                        |
| Mixed Connective Tissue Disease, no. (%)           |            |                   |                  |                        |
| Antiphospholipid Syndrome, no. (%)                 |            |                   |                  |                        |
| Treatment:                                  |            |                   |                  |                        |
| Corticosteroid ever, no. (%)                       |            |                   |                  |                        |
| Corticosteroid current, no. (%)                    |            |                   |                  |                        |
| Hydroxychloroquine ever, no. (%)                   |            |                   |                  |                        |
| Hydroxychloroquine current, no. (%)                |            |                   |                  |                        |
| Other csDMARDs ever, no. (%)                       |            |                   |                  |                        |
| Other csDMARDs current, no. (%)                    |            |                   |                  |                        |
| BioDMARDs ever, no. (%)                            |            |                   |                  |                        |
| BioDMARDs current, no. (%)                         |            |                   |                  |                        |
| Clinical findings:                          |            |                   |                  |                        |
| EULAR/ACR 2019 classification criteria, score 0-51 |            |                   |                  |                        |
| Constitutional*, score 0-2                         |            |                   |                  |                        |
| Haematological*, score 0-4                         |            |                   |                  |                        |
| Neuropsychiatric*, score 0-5                       |            |                   |                  |                        |
| Mucocutaneous*, score 0-6                          |            |                   |                  |                        |
| Serosal*, score 0-6                                |            |                   |                  |                        |
| Musculoskeletal*, score 0-6                        |            |                   |                  |                        |
| Renal*, score 0-4                                  |            |                   |                  |                        |
| Blood samples:                              |            |                   |                  |                        |
| APL positive* ever, score 0-2                      |            |                   |                  |                        |
| Complement low* ever, score 0-4                    |            |                   |                  |                        |
| dsDNA /Smith elevated* ever, score 0-6             |            |                   |                  |                        |
| SLICC 2012 classification criteria, score 0-17     |            |                   |                  |                        |
| ACR 1997 classification criteria, score 0-11       |            |                   |                  |                        |

Value will be means and SDs unless otherwise indicated. \*According to EULAR/ACR 2019 classification criteria (15). PD – Pulmonary Disease according to multidisciplinary discussion; BMI – Body Mass Index; CTD – Connective tissue disease; csDMARD – Conventional Disease-Modifying Antirheumatic Drugs; bioDMARDs – Biologic Disease-Modifying Antirheumatic Drugs. APL– Antiphospholipid Antibodies; dsDNA – anti-double stranded DNA antibodies. The reported Standardised

Difference is the difference between PD present and PD absent, standardised deviation based on the standard deviation for continuous outcomes measures.

**Table 2.** Systemic Lupus Erythematosus activity and damage scores, patient reported outcome measures, pulmonary function tests, for all patients and stratified according to presence and absence of pulmonary disease.

| SLE scores, PROMs, and PFT outcomes      | All | PD Present | PD Absent | Contrast between groups (95%CI) |
|------------------------------------------|-----|------------|-----------|---------------------------------|
| SLE disease specific score:       |     |            |           |                                 |
| SLEDAI 2K, score 0-105                   |     |            |           |                                 |
| SLEDAI 2K, without PD, score 0-103       |     |            |           |                                 |
| PGA, score 0-3                           |     |            |           |                                 |
| LLDAS achieved no. (%)                   |     |            |           |                                 |
| DORIS remission achieved no. (%)         |     |            |           |                                 |
| SLICC DI, score 0-48                     |     |            |           |                                 |
| SLICC DI, without PD, score 0-43         |     |            |           |                                 |
| PROMs:                            |     |            |           |                                 |
| LIT, score 0-100                         |     |            |           |                                 |
| SLAQ, score 0-100                        |     |            |           |                                 |
| MRC, score 1-5                           |     |            |           |                                 |
| Dry cough, composite                     |     |            |           |                                 |
| Dry cough, status                        |     |            |           |                                 |
| Never, no. (%)                           |     |            |           |                                 |
| Prior, no. (%)                           |     |            |           |                                 |
| Present, no. (%)                         |     |            |           |                                 |
| Tightness in chest, composite            |     |            |           |                                 |
| Tightness in chest, status               |     |            |           |                                 |
| Never, no. (%)                           |     |            |           |                                 |
| Prior, no. (%)                           |     |            |           |                                 |
| Present, no. (%)                         |     |            |           |                                 |
| Pulmonary function tests:         |     |            |           |                                 |
| Body plethysmography:             |     |            |           |                                 |
| FEV 1 , %*                    |     |            |           |                                 |
| FEV 1 low**, no. (%)          |     |            |           |                                 |
| FVC, %*                                  |     |            |           |                                 |
| FVC low**, no. (%)                       |     |            |           |                                 |
| FEV 1 /FVC (ratio)            |     |            |           |                                 |
| FEV 1 /FVC below 70%, no. (%) |     |            |           |                                 |
| TLC, %*                                  |     |            |           |                                 |
| TLC low**, no. (%)                       |     |            |           |                                 |
| Diffusion test:                   |     |            |           |                                 |
| DLCO, %*                                 |     |            |           |                                 |
| DLCO low**, no. (%)                      |     |            |           |                                 |
| KCO, %*                                  |     |            |           |                                 |
| KCO low**, no. (%)                       |     |            |           |                                 |
| 6 min walk test:                  |     |            |           |                                 |
| Distance, %*                             |     |            |           |                                 |
| Distance low**, no. %                    |     |            |           |                                 |
| Desaturation, (Saturation delta)         |     |            |           |                                 |
| Desaturation below 93% #, no. %          |     |            |           |                                 |

Value will be means and SDs unless otherwise indicated. \* - % of expected; \*\* - low is defined as below 80% of expected; # - If COPD or emphysema 88%. SLE – Systemic Lupus Erythematosus; PROMs – Patient Reported Outcome Measures; PFT – Pulmonary Function Tests; PD – Pulmonary Disease according to multidisciplinary discussion; APL– Antiphospholipid Antibodies; dsDNA – anti-double stranded DNA antibodies; SLEDAI 2K – Systemic Lupus Erythematosus Disease Activity Index 2000 (16); PGA – Physician Global Assessment (17); LLDAS – Lupus Low Disease Activity State (18); DORIS – Definition of

Remission in SLE (19); SLICC DI – Systemic Lupus International Collaborating Clinics /American College of Rheumatology Damage Index for Systemic Lupus Erythematosus (20); LIT – questionnaire inspired by “Lupus Impact Tracker” (21); SLAQ – Systemic Lupus Activity Questionnaire (22); MRC – Medical Research Council Dyspnoea Scale; FEV1 – Forced Expiratory Volume in One Second; FVC – Forced Vital Capacity; TLC – Total Lung Capacity; DLCO - Diffusing capacity of the Lung for Carbon Monoxide; KCO – Carbon Monoxide Transfer Coefficient.

We plan to present the prevalence of subgroups of PD in a table, see table 3.

**Table 3.** Diagnoses of pulmonary diseases among Systemic Lupus Erythematosus patients.

| Groups of PD | Subgroups of PD                 | Prevalence, no. (%) |
|--------------|---------------------------------|---------------------|
| Airway       |                                 |                     |
|              | Asthma                          |                     |
|              | Bronchiectasis                  |                     |
|              | Obliterative Bronchiolitis      |                     |
|              | Infectious Bronchiolitis        |                     |
|              | COPD                            |                     |
|              | Emphysema                       |                     |
|              | Other                           |                     |
| Pleural      |                                 |                     |
|              | Pleuritis                       |                     |
|              | Pleural disease of diaphragm    |                     |
|              | Pleuroparenchymal fibrosis      |                     |
|              | Other                           |                     |
| ILD          |                                 |                     |
|              | UIP                             |                     |
|              | Probable UIP                    |                     |
|              | Indeterminate for UIP           |                     |
|              | NSIP, fibrotic                  |                     |
|              | NSIP, non-fibrotic              |                     |
|              | HP fibrotic                     |                     |
|              | HP non-fibrotic                 |                     |
|              | Pneumonitis                     |                     |
|              | Diffuse alveolar haemorrhage    |                     |
|              | LIP                             |                     |
|              | OP                              |                     |
|              | Other                           |                     |
| SLS          |                                 |                     |
| Vascular     |                                 |                     |
|              | Pulmonary embolism              |                     |
|              | Pulmonary arterial hypertension |                     |
|              | Pulmonary vasculitis            |                     |
|              | Other                           |                     |
| Other        |                                 |                     |
|              | Atelectasis                     |                     |
|              | Infections                      |                     |
|              | Thoracic malignancy             |                     |
|              | Other                           |                     |

PD – Pulmonary Disease; COPD – Chronic Obstructive Pulmonary Disease; UIP – Usual Interstitial Pneumonia; NSIP – Non-Specific Interstitial Pneumonia; HP – Hypersensitivity Pneumonitis; LIP – Lymphoid Interstitial Pneumonia; OP – Organising Pneumonia; SLS – Shrinking Lung Syndrome. The percentage is of the total study population.

We plan to present results of PFT test of subtypes of PD (Airway disease, Pleural Disease, ILD, and SLS) and the contrast between groups with means, SD, and a 95% confidence interval for continues data or number and percentages for categorical data in appendixes, see Appendix 1 a-d.

We plan to present the prevalence of High-Resolution CT findings among the investigated study population is presented in an appendix, see appendix 2.

We plan to present results of the univariate logistic analyses, with Odds Ratio and corresponding 95%CI, of the association between selected baseline characteristics and the presence of PD, airway disease, pleural disease, ILD, and SLS in a table, see table 4.

**Table 4.** Impact of selected baseline characteristics and patient related outcome measures in groups of thoracic diseases investigated by univariate logistic regression analyses.

| PD Outcome
vs.
Baseline characteristics | PD
Odds
Ratio
(95%CI) | Airway
Odds
Ratio
(95%CI) | Pleural
Odds
Ratio
(95%CI) | ILD
Odds
Ratio
(95%CI) | SLS
Odds
Ratio
(95%CI) |
|--------------------------------------------------------|------------------------------------------|----------------------------------------------|-----------------------------------------------|-------------------------------------------|-------------------------------------------|
| Age, years                                             |                                          |                                              |                                               |                                           |                                           |
| Female sex, no (%)                                     |                                          |                                              |                                               |                                           |                                           |
| Disease duration, years                                |                                          |                                              |                                               |                                           |                                           |
| Smoking, composite                                     |                                          |                                              |                                               |                                           |                                           |
| Smoking, status                                        |                                          |                                              |                                               |                                           |                                           |
| Never, no. (%)                                         |                                          |                                              |                                               |                                           |                                           |
| Prior, no. (%)                                         |                                          |                                              |                                               |                                           |                                           |
| Present no. (%)                                        |                                          |                                              |                                               |                                           |                                           |
| Overlap to other CTDs, composite, no. (%)              |                                          |                                              |                                               |                                           |                                           |
| Overlap to other CTDs, no. (%)                         |                                          |                                              |                                               |                                           |                                           |
| Sjogren's Syndrome, no. (%)                            |                                          |                                              |                                               |                                           |                                           |
| Rheumatoid Arthritis, no. (%)                          |                                          |                                              |                                               |                                           |                                           |
| Systemic Sclerosis, no. (%)                            |                                          |                                              |                                               |                                           |                                           |
| Mixed Connective Tissue Disease, no. (%)               |                                          |                                              |                                               |                                           |                                           |
| Antiphospholipid Syndrome, no. (%)                     |                                          |                                              |                                               |                                           |                                           |
| Pleuritis, positive, no. (%)                           | /                                        |                                              | /                                             |                                           |                                           |
| Pleural effusion, no. (%)                              | /                                        |                                              | /                                             |                                           |                                           |
| Positive APL ever, no. (%)                             |                                          |                                              |                                               |                                           |                                           |
| Decreased complement ever, no. (%)                     |                                          |                                              |                                               |                                           |                                           |
